### Phase 2: pilot feasibility testing of CaCBT

#### Pilot test the newly developed CaCBT for feasibility, acceptability and effectiveness via quantitative methodology and a randomized controlled trial

##### Methods

The newly developed CaCBT will be pilot tested for feasibility, acceptability and effectiveness and compared to standard CBT at three sites in Canada (GTA, Ottawa and Vancouver). A randomized controlled assessor-blind clinical trial will compare CaCBT with standard CBT.

Participants who meet the inclusion criteria will be randomly allocated to one of two groups at each site: CaCBT (experimental group) or standard CBT (control group) in a 1:1 ratio. The experimental group will receive 8–12 weekly sessions of the newly developed CaCBT while the control group will receive 8–12 weekly sessions of standard CBT. Therapists providing both CaCBT and standard CBT will be trained to ensure the fidelity of the therapies being offered.

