##### Sample size calculation

The sample size was calculated using a comparison between group change in the HADS Depression subscale scores. With a 5% significance level and 90% power, we determined that 48 subjects per group will be required for the trial, in order to detect a standardized effect size Cohen’s *d* = 0.68, which is equivalent to a difference in HADS score at the end of the trial of around 2.4 points, assuming a standard deviation of 3.5 found in previous studies from our lab that used the same outcome. To account for up to 30% attrition, we plan to recruit a total of 140 participants into the study.

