
For the economic evaluation, an incremental cost-effectiveness analysis will be carried out to estimate the cost-effectiveness (C/E) ratio associated with the CaCBT programme according to published guidelines [53, 54]. The costs incurred during the study period (3 and 9 months) will be accounted for in both experimental arms. Effectiveness will be considered based on a 25% decrease in HADS and improvement (yes/no) in WHODAS scores between baseline and the 3-month and 9-month observation periods. The C/E ratio will be calculated for the 3-month and 9-month observation periods as follows: [average costs (CaCBT group) – average costs (control group)]/[# of improvements in CaCBT group − # of improvements in control group]. This will report the additional average costs associated with one improved case associated with the programme. Treatment groups will be compared with respect to baseline characteristics (age, sex) as well as scores on the HADS, WHODAS and health service utilization in the previous 6 months such as the number of outpatient and emergency department visits and hospitalizations and follow-up and adherence to programme. This will elucidate whether these factors will need to be considered in the analyses and interpretation of C/E results. Sensitivity analyses will also be carried out to test the robustness of the results.

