## Discussion

Research shows high rates of depression and anxiety among SA Canadians. This group also has lower rates of access to mental health care and has poorer outcomes. There are a number of psychosocial treatments available for depression and anxiety, but to the best of our knowledge, there has been no trial of any evidence-based intervention in this hard-to-reach group in Canada. As such, this is the first trial of culturally adapted CBT for South Asians in North America and Europe. This paper describes the development and testing of culturally adapted CBT. As far as we are aware, this is the first fully powered trial to compare culturally adapted CBT with standard CBT and to conduct an economic evaluation.

The impact of this intervention on service users will be to improve their mental health literacy and improve their self management capabilities through CBT. This may lead to improvement in their well-being and improve their satisfaction with health services as well as improvements in relationships, quality of life and functioning. We are undertaking a detailed process of culturally tailoring this intervention to the specific needs of our target population. This will not only help in improved efficacy but will possibly lead to fewer dropouts and higher satisfaction. The results of this study will be shared widely. Using an integrated dissemination plan, the results of the various stages will be shared through a variety of means including a launch event, webinars, manuscripts and policy reports.

The outcome of this trial will benefit health services in Canada, in terms of helping to reduce the burden of depression and anxiety and provide better care for South Asians. We expect the results to help guide the development of better services and tailor existing services to the needs of other hard-to-reach and vulnerable groups and for other cultural populations.

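### The cost-effectiveness ratio divides by a raw count of improved participants, so unless missing outcomes are imputed its denominator moves with retention

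*Protocol article*

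**What the plan says.** The economic paragraph of the Statistical analyses section (Protocol article, Phase 2) makes effectiveness a yes/no outcome: "Effectiveness will be considered based on a 25% decrease in HADS and improvement (yes/no) in WHODAS scores between baseline" and each follow-up. It then gives an explicit formula for the 3- and 9-month horizons. The numerator is average cost with CaCBT minus average cost in the control group. The denominator is the number "of improvements in CaCBT group" minus the number in the control group. The result is described as the extra average cost of one improved case.

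Three other places bear on the point:

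- **Attrition.** Sample size calculation: "To account for up to 30% attrition, we plan to recruit a total of 140 participants into the study". No split by arm is given.
- **Source of costs.** Under Measurements, service use and out-of-pocket costs come from participant questionnaires. Programme costs (training, sessions, salaries, overhead) do not depend on them.
- **Dropout.** The clinical part of Statistical analyses uses a maximum-likelihood mixed model under missing at random (MAR), with weighted completer and last-observation-carried-forward analyses as support. All are described for the HADS score. The economic paragraph names no method for missing responder status or costs. It does plan to compare the arms on follow-up and adherence, and to run sensitivity analyses whose content is not given.

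**The concern.** A count of improvements is the product of three things: the number randomised, the fraction assessed and the fraction of those who improved. Only the last is a treatment effect on symptoms or disability. If missing outcomes are not filled in, a lost participant adds nothing to the count, while the questionnaire-based part of the average cost is taken over those who returned a questionnaire. The two halves of the ratio then describe different groups of people.

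Equal loss in both arms shrinks the denominator and raises the apparent cost per improved case. Unequal loss can add or remove cases with no difference in response. The authors think fewer dropouts under CaCBT are possible: "This will not only help in improved efficacy but will possibly lead to fewer dropouts and higher satisfaction". The economic evaluation is a stated secondary objective, so its main result should not partly measure retention.

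**Working it through.** **Inputs from the Protocol article**

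- Sample size calculation: "With a 5% significance level and 90% power, we determined that 48 subjects per group will be required for the trial"; standardised effect 0.68, "equivalent to a difference in HADS score at the end of the trial of around 2.4 points", with an assumed SD of 3.5; up to 30% attrition; 140 recruited.
- Phase 2 Methods: "CaCBT (experimental group) or standard CBT (control group) in a 1:1 ratio", so 140/2 = 70 per arm.

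**Assumptions (not in the documents).** Response rates, retention by arm, and dropout unrelated to response.

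**Step 1: the plan's own figures.** With d = 0.68, two-sided 5% and 90% power, the normal formula gives 46 per arm and the t-test version 46.4, so 47. The stated 48 is consistent (t-test power at 48 per arm is 0.909). For attrition, 48/0.70 = 68.6, so 69 per arm and 138 in total, against 140 stated. Using 70 per arm is therefore reasonable. The economic paragraph gives a formula but no numerical result to reproduce.

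**Step 2: the denominator when only observed improvements are counted.**

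Count difference = 70 × (r₁p₁ − r₀p₀), where r is the fraction assessed, p the true response rate, and 1 = CaCBT, 0 = control. The target with full follow-up is 70 × (p₁ − p₀).

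| True response | Retention CaCBT / CBT | Counts | Difference | Target |
|---|---|---|---|---|
| 60% v 50% | 70 / 70 | 29.4 v 24.5 | 4.9 | 7 |
| 60% v 50% | 75 / 65 | 31.5 v 22.75 | 8.75 | 7 |
| 60% v 50% | 80 / 60 | 33.6 v 21 | 12.6 | 7 |
| 60% v 50% | 65 / 75 | 27.3 v 26.25 | 1.05 | 7 |
| 50% v 50% | 70 / 70 | 24.5 v 24.5 | 0 | 0 |
| 50% v 50% | 75 / 65 | 26.25 v 22.75 | 3.5 | 0 |
| 50% v 50% | 80 / 60 | 28 v 21 | 7 | 0 |

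Relative to 7, the first three rows are 30% too low (4.9/7 = 0.70), 25% too high (8.75/7 = 1.25) and 80% too high (12.6/7 = 1.80). For a fixed cost difference the ratio is multiplied by the inverse: 1.43, 0.80 and 0.56.

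**Step 3: range over the response rate with no true effect.** At common response rates of 30% to 60%, the spurious difference is 2.1 to 4.2 cases for 75/65 retention and 4.2 to 8.4 for 80/60.

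**Step 4: proportions instead of counts.** Under the same assumptions, the proportion improved among those assessed gives 0.60 − 0.50 = 0.10 and 0.50 − 0.50 = 0 at every retention split. In these examples, then, the distortion comes from counting. Imputation matters when dropout is related to response, which this calculation does not cover.

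**Step 5: scale.** The formula also divides a per-person cost by a whole-arm count. For an illustrative cost difference of 500 units and complete follow-up, 500/7 = 71, whereas the cost per improved case is 500/0.10 = 5,000. The factor is 70, the arm size. Changing to proportions corrects this too.

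**The case against.** The strongest reply is that this argues from silence. A condensed article may leave missing-data rules for a secondary economic analysis to the full protocol or SAP, and the counts could be taken from imputed data. That stands in part: the absence of an economic missing-data rule is not, by itself, a finding. What remains is the formula the article does state. It uses counts, and without imputation those depend on how many are assessed.

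A reader might infer more, namely that the plan scores every dropout as a failure, has no valid handling of attrition, and will favour CaCBT. The documents do not support that:

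- Scoring dropouts as not improved is the natural result of an unimputed count, but the article does not say it. It could also be a deliberate choice if declared.
- The 30% is an overall planning ceiling. No differential loss to follow-up is forecast. The Background remark on fewer dropouts concerns leaving therapy, which is not the same as missing an assessment; the Discussion remark can be read the same way.
- Programme costs need not be missing for dropouts, so only part of the numerator is exposed.
- If CaCBT retains fewer people, the bias runs against it.

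It is also fair to say that the article plans to compare follow-up by arm and promises sensitivity analyses. These could reveal a retention gap. Neither changes the formula or names a method to apply if a gap is found.

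**Conclusion.** The point holds for the formula as written. With a count in the denominator and no imputation, the ratio varies with retention under the plan's own attrition allowance. For a true difference of 7 cases in 70 per arm, the denominator is 4.9 under equal 30% loss, and 8.75 or 12.6 under the two splits favouring CaCBT. With no true difference, those splits create 3.5 or 7 cases. Equal loss creates no false cases; it only dilutes a real difference.

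The retention splits and response rates are assumed, and dropout is taken as unrelated to response. The size and direction of the error in this trial therefore cannot be known from the documents. The conclusion is that the effect measure and its population need to be redefined. It is not that the economic result will be biased in a known direction.

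**What to change.** In the economic paragraph of Statistical analyses:

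1. Replace the number improved with the proportion improved in each arm.
2. Compute mean costs and proportion improved on the same population, all randomised participants, at each of the 3- and 9-month horizons.
3. Multiply impute missing HADS, WHODAS and questionnaire-based costs by arm, under the MAR assumption the clinical analysis already makes. Derive the 25% HADS reduction and the WHODAS improvement after imputation. Programme costs can be entered from study records.
4. Report a complete-case version and a version with dropout counted as not improved, both labelled as sensitivity analyses.

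The cost is a change of wording and some extra analysis. No new data or participants are needed. The drawback is reliance on MAR, which the sensitivity analyses in item 4 would help to probe.

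### The cost-effectiveness ratio divides a per-participant cost difference by a difference in head counts, so with equal arms it gives the cost per improved case divided by the arm size

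*Protocol article*

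**What the plan says.** In the protocol article, Methods, Phase 2, Statistical analyses, the economic paragraph builds the ratio from these parts:

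- **Numerator:** "average costs (CaCBT group) – average costs (control group", a difference between two arm means.
- **Denominator:** the number "of improvements in CaCBT group − # of improvements in control group", a difference between two counts.
- **How they are joined:** the first is divided directly by the second, "average costs (control group)]/[# of improvements in CaCBT group".
- **What is counted:** "Effectiveness will be considered based on a 25% decrease in HADS and improvement (yes/no) in WHODAS scores". Each participant is thus classed as improved or not, at 3 and at 9 months.
- **Meaning given to the result:** "This will report the additional average costs associated with one improved case associated with the programme".

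The scale of the two arms comes from other sections. Allocation is to "CaCBT (experimental group) or standard CBT (control group) in a 1:1 ratio" (Phase 2, Methods). Under Sample size calculation, "48 subjects per group will be required for the trial", with 140 to be recruited in total to allow for attrition of up to 30%. The economic evaluation is secondary objective (b) under Aims and objectives.

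**The concern.** A mean cost is in dollars per participant. A count of improvements belongs to the whole arm and grows with the number of people in it. Dividing one by the other does not give dollars per improved case, which is what the next sentence says it gives. Nothing in the article turns the counts into proportions or the mean costs into arm totals. The formula and its stated meaning therefore contradict each other.

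At stake is the summary figure of a stated secondary objective. The Discussion gives the economic evaluation prominence and plans policy reports. An analyst who applied the printed formula literally would report a cost per improved case wrong by more than one order of magnitude.

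**Working it through.** **1. Arm size, which sets the scale of the error.** The plan states no numerical cost-effectiveness ratio, so the figure to reproduce is the arm size. The inputs, from Sample size calculation, are d = 0.68 (2.4 points, SD 3.5), "With a 5% significance level and 90% power", and 30% attrition. Sidedness is not stated; two-sided is assumed.

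- Normal approximation: n = 2 × (1.960 + 1.282)² / 0.68² = 45.5, so 46 per arm. The t-based calculation gives 46.4, so 47. The plan's 48 is slightly above both.
- Recruitment: 2 × 48 / 0.70 = 137.1, so 138. The plan's 140 covers this.
- Arm sizes for what follows: 140 / 2 = 70 randomised; 140 × 0.70 / 2 = 49 after 30% attrition; 48 as the required number.

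**2. The formula with equal arms.** Let D be the difference in mean cost per participant, x1 and x0 the improved counts (CaCBT, standard CBT), and n the number analysed in each arm.

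- Printed formula: D / (x1 − x0).
- Cost per additional improved case: D / (x1/n − x0/n) = n × D / (x1 − x0).
- The second is n times the first. D, x1 and x0 cancel, so the factor of n needs no assumption about costs or improvement rates.

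**3. Illustration.** The costs and rates are assumed: D = 1,000 dollars, with about 60% against 40% improved.

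| Analysed per arm | Improved | As printed | Cost per improved case | Factor |
|---|---|---|---|---|
| 70 | 42 v 28 | 1000/14 = 71.43 | 1000/0.20 = 5,000 | 70 |
| 49 | 29 v 20 | 1000/9 = 111.11 | 1000/(9/49) = 5,444 | 49 |
| 48 | 29 v 19 | 1000/10 = 100 | 1000/(10/48) = 4,800 | 48 |

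If CaCBT were instead 1,000 dollars cheaper, with 42 v 28 improved out of 70, the printed formula would show a saving of 71.43 dollars per improved case where the correct figure is 5,000.

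**4. Unequal analysed arms (hypothetical).** With n1 and n0 analysed and proportions p1 and p0 improved, the factor is (n1·p1 − n0·p0)/(p1 − p0) = n1 + (n1 − n0)·p0/(p1 − p0).

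- 70 v 60 analysed, 60% v 40%: 70 + 10 × 0.40/0.20 = 90.
- 72 v 68 analysed, 43 v 27 improved: (43 − 27)/(43/72 − 27/68) = 79.9.
- 70 v 55 analysed, 28 v 24 improved: the counts differ by +4, but the proportions are 40.0% and 43.6%, a difference of −3.6 percentage points. With D = 1,000 dollars the printed formula gives 1000/4 = 250 dollars per improved case, although here CaCBT costs more and improves a smaller share.

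**The case against.** **It may be shorthand.** The article is condensed, cites published guidelines for the analysis, and names the quantity it wants. A health economist could read the count as improvements per participant. That makes it less likely that the wrong number is ever reported. It does not repair the text, which prints an explicit formula with averages above and counts below.

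**It is secondary and recoverable.** This stands. The formula does not touch randomisation, data collection, sample size or the primary analysis. Costs, HADS and WHODAS are collected the same way whichever denominator is used, and no ratio has yet been reported.

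**A reader might infer that the formula necessarily favours CaCBT.** The documents do not support that, because they give no expected cost difference. Only the error in absolute scale is established.

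**A reader might also infer that better retention under CaCBT will distort the count or flip its sign.** The article says only that CaCBT can reduce dropouts (Background) and will possibly lead to fewer (Discussion). The sign reversal above needs markedly unequal numbers analysed, for example because only assessed participants are counted. It cannot arise when both arms are analysed at the same size. The Statistical analyses section sets intention to treat for the primary analysis, and how the economic analysis treats missing data may properly be left to a fuller plan. The sign reversal is therefore a possibility, not a prediction.

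**Conclusion.** The formula is wrong as written. With equal analysed arms its absolute value is too small by a factor of exactly the arm size: 70 for all randomised participants, about 48 to 49 after 30% attrition. That rests only on 1:1 allocation and the planned numbers.

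The direction of any misleading impression is conditional on the trial's results. A CaCBT that costs more and improves more people would look far cheaper per improved case than it is; a CaCBT that is cheaper and better would have its saving understated. With unequal analysed arms the factor is no longer the arm size, and the denominator's sign is not guaranteed. The consequence is confined to the secondary economic evaluation.

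**What to change.** Redefine the ratio at each time point as:

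[mean cost per participant, CaCBT − mean cost per participant, standard CBT] / [proportion improved, CaCBT − proportion improved, standard CBT]

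State that the same participants enter the numerator and the denominator. The existing sentence on interpretation can then stay.

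Total costs over counts is not a safe substitute. It agrees with this ratio when the arms are equal, but not in general otherwise. With assumed mean costs of 2,500 and 2,000 dollars, 70 v 60 analysed and 42 v 24 improved, it gives (175,000 − 120,000)/18 = 3,056 dollars, against 500/0.20 = 2,500.

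The change is a line or two of wording, with no new data, participants or procedures. It does not settle missing costs or missing improvement status. The mixed model for continuous HADS scores does not supply these, so their handling is a separate matter for the full economic plan.

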The CaCBT programme costs associated with the training of professionals and therapy sessions provided to participants in the CaCBT arm will be considered and will include professional salaries and benefits and institutional overhead and building opportunity costs.

The cost analysis in this study will be carried out from the health system and participant perspectives. Participant costs will be based on the measurement and costing of health resources according to published Canadian guidelines [43] and published methodology in evaluating mental health programmes and attributable costs associated with mental disorders in Canada [44–48].

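### The economic result is stated only as a C/E ratio; it has no finite 95% interval in roughly a quarter of trials at the design effect, and in most trials if the effect over active CBT is small

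*Protocol article*

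**What the plan says.** The Statistical analyses section for Phase 2 fixes the economic summary by formula: "average costs (CaCBT group) – average costs (control group)]/[# of improvements in CaCBT group − # of improvements in control group". On timing it says: "The C/E ratio will be calculated for the 3-month and 9-month observation periods as follows". Two binary outcomes define effect: "Effectiveness will be considered based on a 25% decrease in HADS and improvement (yes/no) in WHODAS scores". The Measurements section adds: "The cost analysis in this study will be carried out from the health system and participant perspectives". There are therefore at least four ratios (two times by two definitions) before the perspectives are counted.

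The ratio is then interpreted in words: "This will report the additional average costs associated with one improved case associated with the programme". On robustness the section says only: "Sensitivity analyses will also be carried out to test the robustness of the results". It also refers to published guidelines for the method. It gives no rule for a denominator that is zero, negative or poorly estimated.

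The trial is sized on a continuous outcome, the HADS Depression subscale, and not on costs or improvement rates. The Sample size calculation section states: "With a 5% significance level and 90% power, we determined that 48 subjects per group will be required for the trial". The effect size behind that number is d = 0.68. Economic evaluation is a named secondary objective under Aims and objectives.

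**The concern.** A ratio of two estimated differences is unstable when the bottom difference is uncertain. Three features of this trial make that relevant.

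- The comparator is active CBT with the same number of sessions, so the difference in improved cases could be modest.
- The denominator uses dichotomised outcomes, which carry less information than the continuous score used for sizing.
- The planned interpretation, a cost per improved case, makes sense only when the effect difference is positive.

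The sign is a further problem. Suppose CaCBT is $500 cheaper and improves 10 percentage points more patients: the ratio is -500/0.10 = -$5,000. Suppose it is $500 dearer and improves 10 points fewer: 500/(-0.10) = -$5,000. These opposite findings share one number. A positive ratio is ambiguous in the same way (dearer and better, or cheaper and worse).

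At stake is a published cost per improved case that may be largely noise, or a negative figure read the wrong way round.

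**Working it through.** **Inputs from the Protocol article.** From Sample size calculation: 5% significance, 90% power, d = 0.68 (about 2.4 points with SD 3.5), 48 per group, 140 recruited, up to 30% attrition. Allocation is 1:1. So 70 are randomised per arm, and 70 x 0.70 = 49 per arm remain after attrition.

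**The plan's own figure.** n = 2(1.96 + 1.2816)² / 0.68² = 45.4, so 46 per arm; the t-test version gives 47. The stated 48 is within two patients. 96/0.70 = 137.1, so 138; the stated total is 140. The sample size reproduces (two-sided test assumed).

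**Assumptions not in the documents.**
- 30%, 40%, 50% or 60% improve under standard CBT.
- The CaCBT rate is p1 = Φ(Φ⁻¹(p0) + d), a shift of d on the probit scale.
- The same d applies to either effectiveness definition.
- The two arms are equal in size, so the difference in counts and the difference in proportions have the same sign.

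**Criterion.** A 95% Fieller interval for the ratio is unbounded when the 95% interval for the denominator includes zero. With SE = √[p0(1-p0)/n + p1(1-p1)/n], that means an estimated difference smaller in size than 1.96 x SE.

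**One case by hand** (p0 = 0.50, d = 0.68, n = 49):
- p1 = Φ(0.68) = 0.752, a difference of 0.252.
- SE = √[(0.250 + 0.186)/49] = 0.094, so the observed difference must exceed 1.96 x 0.094 = 0.185.
- z = 0.252/0.0944 = 2.67.
- P(unbounded) ≈ Φ(1.96 - 2.67) = 0.24; exact binomial calculation gives 0.247.
- P(difference ≤ 0) ≈ Φ(-2.67) = 0.004; exact 0.006.

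**Exact binomial results**, as ranges over control improvement of 30-60%:

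| True d | Denominator ≤ 0, 48-49 per arm | Interval unbounded, 48-49 per arm | Denominator ≤ 0, 70 per arm | Interval unbounded, 70 per arm |
|---|---|---|---|---|
| 0.68 | 0.5-0.9% | 23-29% | 0.1-0.2% | 11-14% |
| 0.5 | 3-4% | 48-52% | 1-2% | 34-37% |
| 0.4 | 7-8% | 64-66% | about 4% | 53-55% |
| 0.3 | 14-15% | 77-78% | 9-10% | 71% |
| 0.2 | 25-26% | 87-88% | about 20% | 84% |

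At d = 0.68 and 48-49 per arm, the count difference falls within two cases of zero in only about 1.4-2.6% of trials. At d = 0.2-0.3 it does so in 20-32%.

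**The case against.** The strongest reply is that this is a condensed article. Methods for uncertainty in a cost-effectiveness ratio are ordinary content of a full protocol or analysis plan, the cited guidelines may prescribe them, and the promised sensitivity analyses could include resampling. This stands in part: the absence of a named interval method would not by itself be a finding, and nothing shown excludes intervals. But the article does choose the summary statistic and its interpretation. An interval added later to this ratio may not exist as a finite range, so the choice itself deserves attention.

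It can also be said that the formula needs each arm's mean cost and number improved, and that showing these would settle the sign. That is correct, and it is part of the fix; the article does not say they will be reported.

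A reader might infer three stronger things that the documents do not support.

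- That everything rests on a single ratio. There are at least four.
- That the denominator will often be near or below zero at this sample size. At the protocol's own design effect it is at or below zero in under 1% of trials; higher frequencies need a true effect well below d = 0.68.
- That the ratio has no finite interval as a rule. It lacks one only when the interval for the effect difference includes zero, which at the design effect is a minority of trials.

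Dividing a mean cost difference by a difference in counts is a separate units problem. Correcting it would not cure the instability described here.

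**Conclusion.** The point holds as a conditional one and should be addressed. The only economic result stated is a ratio whose precision is not assured by the trial's sizing. Even if the planned effect is true, about one trial in four with 48-49 assessed per arm would yield no finite 95% interval. If the advantage over active CBT is small, that becomes the usual outcome, and a zero or negative denominator becomes a real possibility. Without its two components beside it, a negative ratio is then uninterpretable.

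The sizes rest on assumed control improvement rates, the probit mapping, equal arms, and the same effect on HADS and WHODAS improvement; the documents give none of these. Across 30-60% control improvement the figures move little. The true effect size matters far more, and it is unknown. The consequence is confined to a secondary objective.

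**What to change.** For each time point and effectiveness definition, report the difference in mean cost and the difference in proportion improved separately, each with a 95% interval.

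Make incremental net benefit the economic result: λ x (difference in proportion improved) - (difference in mean cost), over a stated range of λ, the value placed on one improved case. It involves no division, so it has an ordinary interval and an unambiguous sign. Obtain intervals by bootstrapping patients within arm and site, and show a cost-effectiveness plane or acceptability curve.

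The ratio may still be shown as a descriptive figure beside its two components. It should not be interpreted as a cost per improved case when the effect difference is zero or negative. Whether it is reported should not depend on statistical significance, because the ratios that survived such a filter would be selected for overestimated effects.

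The cost is analysis work on data already planned for collection. The downside is that a range of values per improved case must be stated, and the result will look less certain than a ratio alone.
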